## **Clinical assessments**

- **Patient-controlled morphine consumption**:
  - Number of bolus doses delivered in the period 0-8 hours postoperatively is recorded
  - Number of bolus doses delivered in the period 0-24 hours postoperatively is recorded
- **Pain:**
  - Patients' pain is recorded on a Visual Analogue Scale (VAS) of 100 mm, where 0 = no pain and 100 = worst possible pain. Patients state their own pain intensity.
  - Pain is recorded at rest and in connection with 45 degrees active flexion of the knee.
  - Pain is recorded preoperatively before administration of medication, as well as 1, 2, 4, 6, 8 and 24 hours postoperatively, corresponding to the end of the trial period.
- **Side effects:**
  - Nausea and sedation are recorded on a verbal scale (none, mild, moderate, severe) 1, 2, 4, 6, 8 and 24 hours post-operatively.
  - The number of productive vomiting events (volume estimated over 10 ml) is recorded corresponding to the periods 0-1, 1-2, 2-4, 4-6, 6-8 and 8-24 hours post-operatively by interview with the patient.
  - The patient's use of Zofran (mg) 0-8 and 0-24 hours postoperatively is recorded.

The study extends for each patient from introductory conversation to 24 hours postoperatively. The patient receives the above treatments in accordance with a computer-generated randomized list.

# **MEDICATION AND MEDICATION ADMINISTRATION**

## **Study medication**

Active preparation: **Ropivacaine 0.75%.**

Dispensed in the form of injection solution for perineural and epidural use. Contains: ropivacaine hydrochloride monohydrate. In addition, sodium chloride, hydrochloric acid and sodium hydroxide. Water for injection.

The preparation is imported to Denmark by: AstraZeneca A/S, [name]

Holder of marketing authorisation: AstraZeneca A/S, marketing authorisation number 17973.

Active preparation: **Ropivacaine 0.2%.**

Dispensed in the form of infusion solution for perineural and epidural use. Contains: ropivacaine hydrochloride monohydrate. In addition, sodium chloride, hydrochloric acid and sodium hydroxide. Water for injection.

The preparation is imported to Denmark by: AstraZeneca A/S, [name]

Holder of marketing authorisation: AstraZeneca A/S, marketing authorisation number 17971.

Placebo: Sodium chloride 9 mg/ml. Infusion liquid, infusion. 1 litre contains 9 g of sodium chloride in sterile water. Electrolyte/l: 154 mmol chloride and 154 mmol sodium. Isotonic. Osmolarity of approx. 308 mmol/l

## **Blinding procedure, packaging and labeling**

## **Blinding procedure, packaging and labeling**

The study is performed as a double-blind randomized study. Randomisation will be performed by the Capital Region Pharmacy. The experimental medicine will be packed and labelled by the Capital Region Pharmacy. in accordance with the rules for this. Each patient receives medication as indicated below under **"General treatment plan and medication dosage"**. Ropivacaine 0.75% or placebo are blinded by being packaged in one blinded closed cardboard box. The cardboard box is handed over to a person not involved in the trial, who records the batch number and expiry date. This person then draws the medicine into a neutral spray and returns it to the patient's anaesthesia personnel for administration. 2 sets of additional sealed code envelopes are prepared. These contain information about which treatment each of the subjects is being randomly assigned. One set is retained by the sponsor, while the other is retained by the investigator at the Department of Anaesthesia, HOC, Rigshospitalet, in a secure locked place. Capital Region Pharmacy retains the non-blinded randomization list, which will only be sent to the investigator when the data has been analysed.

## **Other treatment**

Other medications that are considered necessary for the subject will be given at the discretion of the investigator.

Administration of all other medical treatment will be recorded on the accompanying Case Report Form.

## **Procedures in case of emergencies**

The investigator will ensure that there are the necessary procedures and expertise to tackle an emergency situation that may arise during the study.

The blinding may only be broken if the continued treatment of the patient requires knowledge of the randomization code. If the code envelope is opened, the date and reason shall be recorded and the envelope signed by the investigator. This results in the exclusion of the patient.

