## **Reasons for patients' withdrawal from the trial**

A patient can be withdrawn from the trial under the following conditions:

- If the investigator believes that a change of treatment will be best for the patient
- If the patient wishes to withdraw from the trial
- Violation of protocol rules

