# **SIDE EFFECTS**

## **Side effects/adverse events (AEs)**

Side effects are defined as any adverse event, signs or symptoms that occur during participation in the study which are time related to the administration of the study medication, whether the adverse event is considered to be related to the study medication or not. All adverse events must be recorded in the patient's Case Report Forms. If an adverse event occurs more than 24 hours after the last administration of the study medication, and there is no apparent causal connection or relation to the study medication, this shall not be deemed to be an adverse event.

Start and end date/time, severity and effects after the study medication must be recorded for all incidents. The severity of the adverse event and the relationship with the study medication must be assessed in accordance with the guidelines described below.

The investigator must assess the relationship between an adverse event and the study medication using the following guidelines:

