# **STATISTICAL ANALYSES**

## **Calculation of the number of patients**

Results from previous studies suggest that all patients will have pain postoperatively. Average pain scores (VAS) for activity (45 degree flexion of knee) in the first 24 hours based on previous studies is typically around 75 (SD 20) (8). We assess that a reduction of 20 in the pain score (VAS) will be clinically relevant.

With a type 1 failure risk of 5% and a type 2 failure risk of 20%, a total of 34 patients, i.e. 17 in each group, will be required.

It is planned to include a total of 34 evaluable patients in the measure of main effect. To compensate for drop-outs it is aimed to include 36 patients.

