## **Data processing**

The trial will be completed when 34 evaluable patients are included in the study.

The evaluability of each patient in the statistical analyses will be decided before the code is broken. Only subjects for whom data for pain scores at 45 degrees flexion of the knee 0-8 hours postoperatively is available will be included in the statistical analysis. Excluded patients and missing, unused or false data will be described. Data will be stored and evaluation and statistical analysis will be made by computer, where patient anonymity will be preserved and local data legislation will be observed.

Results will be described with mean values and standard deviation of the mean value, as well as median and inter-quartile values. A 5% level of significance will be used. Binomial data will be analysed with Fisher's exact test and ratio-interval data with the Mann-Whitney test. Multiple analyses will be adjusted with the Bonferroni test. Pain scores will be compared with the AUC calculation. Any change to the statistical plan will be accounted for by publication.

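### Opening a patient's code leads to an exclusion of unstated scope, most naturally read as removal from the efficacy comparison even when the pain scores were obtained blind

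*Protocol*

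**What the plan says.** Procedures in case of emergencies sets the trigger: "The blinding may only be broken if the continued treatment of the patient requires knowledge of the randomization code". The date and reason must be recorded and the envelope signed. The consequence follows: "This results in the exclusion of the patient". The section does not say whether this means exclusion from further trial treatment, from participation, or from the statistical analysis.

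Data processing defines who is analysed: "Only subjects for whom data for pain scores at 45 degrees flexion of the knee 0-8 hours postoperatively is available will be included". It adds "The evaluability of each patient in the statistical analyses will be decided before the code is broken" and "Excluded patients and missing, unused or false data will be described". No intention-to-treat set is named, and the trial ends once 34 evaluable patients have been included.

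Calculation of the number of patients gives 17 evaluable patients per group and allows for two losses: "To compensate for drop-outs it is aimed to include 36 patients".

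For safety, Side effects/adverse events (AEs) is unconditional: "All adverse events must be recorded in the patient's Case Report Forms". The guidelines on relationship to treatment require every event to be followed up, and the reporting section requires the final report to describe all side effects.

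**The concern.** A code break happens after randomisation and because of the patient's clinical course, so its probability may differ between ropivacaine and placebo. If it removes the patient from the comparison, the patients analysed are partly selected by what happened under treatment. Recruiting a substitute brings the count back to 34 but does not undo that selection.

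The rule also ignores whether usable data exist. Scores recorded before the envelope is opened are as blind as anyone else's. Discarding them costs information and gains no protection against bias.

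**Working it through.** **1. What exclusion most naturally means.** The emergency section leaves the scope open. The statistical section uses the same term for patients who are described, in contrast to those who are analysed, and it recruits until 34 are evaluable. Together these point to removal from the analysis and replacement. This is an inference, because no sentence says it outright.

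**2. The two sections give different answers for the same patient.** The primary endpoint is flexion pain at 4 hours. Pain is recorded at 1, 2, 4, 6, 8 and 24 hours, and the infusion runs from 6 to 24 hours. Take a patient whose code is opened at 12 hours:

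- Under Data processing, the 0-8 hour flexion scores are complete, so the patient is evaluable.
- Under Procedures in case of emergencies, the patient is excluded.

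Every score up to 8 hours, including the primary one, was obtained before the break.

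**3. The blind evaluability decision does not help here.** Deciding evaluability while blind protects against judgements influenced by the assignment. This exclusion involves no judgement. It follows automatically from the code break, and the selection arises from whatever made the break necessary.

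**4. The plan's own sample size.** Inputs from the sample-size section: difference 20, SD 20, alpha 5% (two-sided assumed, as sidedness is not stated), power 80%.

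- Normal approximation: n = 2 × (1.960 + 0.842)² × 20² / 20² = 15.7, so 16 per group and 32 in total.
- Exact t-test with standardised difference 20/20 = 1: n = 16.7, so 17 per group and 34 in total. This reproduces the plan's figure. Power at 17 per group is 80.7%.
- Drop-out allowance: 36 − 34 = 2, and 2/36 = 5.6%. One patient is 1/17 = 5.9% of an arm.

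**5. Effect on power.** Patients are lost from one arm without replacement (t-test, as in step 4):

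| Starting size per group | None lost | 1 lost | 2 lost |
|---|---|---|---|
| 17 | 80.7% | 79.4% | 78.0% |
| 18 | 83.0% | 81.9% | 80.6% |

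The loss is small, and recruiting to 34 makes it good. Power is not the issue.

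**6. Effect on the estimate.** If k of n patients in an arm have scores d mm above the mean of the others, removing them lowers the arm mean by k × d / n. The protocol gives neither k nor d, so both are assumed, with n = 17:

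| Removed (k) | d = 20 mm | d = 40 mm |
|---|---|---|
| 1 | 20/17 = 1.2 mm | 40/17 = 2.4 mm |
| 2 | 40/17 = 2.4 mm | 80/17 = 4.7 mm |

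Against the 20 mm target, one patient accounts for 1.2/20 = 6% to 2.4/20 = 12%. The direction is not known in advance. Removing a high score from the placebo arm shrinks the apparent benefit; removing one from the ropivacaine arm enlarges it. The planned test is rank-based (Mann-Whitney), so these mean shifts only illustrate the scale.

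**The case against.** The strongest objection is that removal from the efficacy analysis is inferred. The only explicit analysis rule rests on data availability, and exclusion in an emergency section could refer to trial treatment or participation alone. That is fair as far as it goes, and it is why the point is put as a reading. But the two sections then need to say so, because as written they disagree about a patient with complete early scores. A statistical analysis plan might add detail, but this is a rule that the protocol states, not a gap left for later.

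It can also be said that code breaks may be rare and the bias small. Both are plausible. The treatment plan provides PCA morphine and further analgesia that can be given without knowing the assignment, so poor pain control alone need not lead to a break.

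Three stronger readings are tempting, and the documents do not support them:

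- **A reader might infer that these patients also vanish from the safety record.** They do not. Adverse events must all be recorded, followed and described in the final report, with no exemption after a code break. Excluded patients are to be described, and the withdrawal section requires an account of non-completers and their data.
- **A reader might infer that the most severe emergencies are the ones removed.** The trigger is the need for the code, not severity. A severe event managed without the code excludes nobody.
- **A reader might extend the point to protocol violators**, since "Violation of protocol rules" is a listed reason for withdrawal. That list says only that a patient can be withdrawn. It does not say that data already collected are discarded.

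**Conclusion.** The concern holds for the efficacy comparison. The natural combined reading is a post-randomisation exclusion that may depend on the assigned arm, applies even to patients with complete blind scores, and is not cured by replacement. It conflicts with the protocol's own availability rule for evaluability.

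The likely effect is modest: about 1.2 to 2.4 mm on an arm mean per excluded patient, if that patient's score lies 20 to 40 mm above the other patients in an arm of 17. That spread is an assumption, and the documents give no code-break rate from which to judge how often it would arise. The planned size of 34 stands, and adverse event reporting is unaffected. The rule should be changed because the correction costs little and removes an avoidable selection.

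**What to change.** In Procedures in case of emergencies, replace the exclusion sentence with wording such as: *Opening the code does not by itself remove a randomised patient from the statistical analysis. Pain scores obtained before the code was opened are analysed in the randomised group. Scores obtained afterwards are flagged and are omitted in a sensitivity analysis.*

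In Data processing, align the evaluability rule by stating that a code break alone does not make a patient non-evaluable. Otherwise the availability rule and the new sentence could still be read against each other.

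If exclusion was meant to cover further trial treatment or participation, say so in a separate sentence. The clinical handling stays as it is.

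The cost is a short edit in two sections, with no change to sample size or data collection. The downside is that a few scores recorded after a break may be unblinded, which the flag and the sensitivity analysis make visible.

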## **Medication accounts**

The investigator will ensure that the study medication is kept in a safe place and only provided to participants in this study. The investigator will ensure that there is strict accounting of the study medication supplied. The investigator shall give an account of any medication that accidentally or otherwise goes missing, and for any discrepancy between the supplied and returned medications.

# **SIDE EFFECTS**

## **Side effects/adverse events (AEs)**

Side effects are defined as any adverse event, signs or symptoms that occur during participation in the study which are time related to the administration of the study medication, whether the adverse event is considered to be related to the study medication or not. All adverse events must be recorded in the patient's Case Report Forms. If an adverse event occurs more than 24 hours after the last administration of the study medication, and there is no apparent causal connection or relation to the study medication, this shall not be deemed to be an adverse event.

Start and end date/time, severity and effects after the study medication must be recorded for all incidents. The severity of the adverse event and the relationship with the study medication must be assessed in accordance with the guidelines described below.

The investigator must assess the relationship between an adverse event and the study medication using the following guidelines:

**Guidelines for adverse events' possible relationship to treatment:**

1. Not related – no temporal relationship, other etiologies are very likely the cause
2. Possibly related – less clear correlation, other etiologies are also possible
3. Probably related – clear temporal correlation with improvement on discontinuation of medication, and not reasonably explained by the patient's known clinical condition.
4. Related – clear temporal relationship with repeated treatment test or clinical assessment.

Patients with adverse events will be monitored with appropriate clinical assessments and laboratory tests according to the decision of the attending doctor. All adverse events will be followed until satisfactory recovery or stabilization.

A serious adverse event (SAE) is understood to be any incident involving a significant risk of the death or disability of the patient (or their offspring), including, but not limited to, an event that results in:

- death
- is life-threatening – in the investigator's opinion the patient was in immediate risk of death from the adverse event when it appeared
- requires hospitalization or prolongs existing hospitalization
- is permanently disabling

- is a congenital anomaly

A summary of product characteristics for Naropin from the Danish Medicines Agency's website will be used as a reference document when it is assessed whether a serious related adverse event is expected or unexpected.

**Grading of adverse events:**

The medical investigator should attempt to identify all clinical and objective reactions from patients in the treatment and determine their relationship with the study medication. Reactions, if there are any, should be graded according to the following scale:

1 = slight

2 = moderate

3 = severe

4 = life-threatening

## **Reporting of side effects of AEs and SAEs**

The investigator is responsible for ensuring that all adverse events are recorded in the patient's Case Report Form.

The sponsor is responsible for ongoing monitoring of the study's risk/benefit relation. If there arise or are seen to be situations that may affect the safety of the study subjects or the performance of the study, these must be **always** immediatelyreported to the Danish Medicines Agency. Similarly, reports should also be made to all investigators and Research Ethics Committees involved.

In addition, the following rules apply for reporting to the authorities. Events and reactions should be included for all study medication – including the experimental treatment, the comparative treatment and any placebo.

The sponsor shall at all time be kept informed by the investigator of any adverse events. At the end of the trial, the final report shall contain a description of all side effects.

Serious adverse events – SAEs - should be reported immediately by the investigatorto the sponsor (sponsor-investigator). SAEs must be reported annually by the Investigator to the Research Ethics Committee throughout the whole trial period, together with a report on the safety of the trial subjects.

Serious adverse reactions – SAR (serious presumed side effects) - shall be reported by the sponsor (sponsor-investigator) annually to the Danish Medicines Agency. The report shall also include a report on the safety of trial subjects.

Suspected unexpected serious adverse reaction – SUSAR (Unexpected and serious side effects) - must be **immediately** reported by the sponsor (sponsor-investigator**)** to the Danish Medicines Agency.

Fatal or life-threatening SUSARs must be reported within **7 days** of the sponsor becoming aware of them, and within **8 days** of the report the sponsor must inform the Danish Medicines Agency of all relevant information on the follow-up.

All other unexpected serious suspected adverse reactions should be reported to the same authorities within 15 days of the sponsor (sponsor-investigator) being informed of these.

All reports must be accompanied by comments on any consequences there are for the trial.

It is also recommended that the sponsor (sponsor-investigator) should inform the manufacturers of the medication.

# **STATISTICAL ANALYSES**

## **Calculation of the number of patients**

Results from previous studies suggest that all patients will have pain postoperatively. Average pain scores (VAS) for activity (45 degree flexion of knee) in the first 24 hours based on previous studies is typically around 75 (SD 20) (8). We assess that a reduction of 20 in the pain score (VAS) will be clinically relevant.

With a type 1 failure risk of 5% and a type 2 failure risk of 20%, a total of 34 patients, i.e. 17 in each group, will be required.

It is planned to include a total of 34 evaluable patients in the measure of main effect. To compensate for drop-outs it is aimed to include 36 patients.

## **Data processing**

The trial will be completed when 34 evaluable patients are included in the study.

The evaluability of each patient in the statistical analyses will be decided before the code is broken. Only subjects for whom data for pain scores at 45 degrees flexion of the knee 0-8 hours postoperatively is available will be included in the statistical analysis. Excluded patients and missing, unused or false data will be described. Data will be stored and evaluation and statistical analysis will be made by computer, where patient anonymity will be preserved and local data legislation will be observed.

Results will be described with mean values and standard deviation of the mean value, as well as median and inter-quartile values. A 5% level of significance will be used. Binomial data will be analysed with Fisher's exact test and ratio-interval data with the Mann-Whitney test. Multiple analyses will be adjusted with the Bonferroni test. Pain scores will be compared with the AUC calculation. Any change to the statistical plan will be accounted for by publication.

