## **Endpoints**

#### Primary end points

- Pain score with 45 degree active flexion of the knee (VAS) 4 hours postoperatively.

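### The evaluability rule requires 0-8 h flexion scores although the primary endpoint needs only the 4 h score, which discards valid primary data and can bias the randomised comparison

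*Protocol*

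**What the plan says.** The primary endpoint is a single value: "Pain score with 45 degree active flexion of the knee (VAS) 4 hours postoperatively" (Primary end points). The measurement schedule is wider: "Pain is recorded preoperatively before administration of medication, as well as 1, 2, 4, 6, 8 and 24 hours postoperatively" (Clinical assessments), so five flexion scores fall within 8 hours of surgery.

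The analysis set is defined under Data processing: "Only subjects for whom data for pain scores at 45 degrees flexion of the knee 0-8 hours postoperatively is available will be included". No other analysis set is named. The same section has evaluability decided before the code is broken, and excluded patients and missing data described. It also sets the end of recruitment: "The trial will be completed when 34 evaluable patients are included in the study".

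Calculation of the number of patients plans 34 evaluable patients and aims to include 36 to cover drop-outs. Separately, Procedures in case of emergencies excludes any patient whose code envelope is opened.

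**The concern.** The set of scores that the rule appears to demand is the set needed for the secondary 1-8 h area under the curve, not the one needed for the primary endpoint. A patient who gives a valid 4 h score but misses the 1, 2, 6 or 8 h score leaves the primary analysis even though the primary outcome was observed.

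Whether a score exists is also decided after randomisation. The patient must actively flex the knee, and pain, sedation or nausea are plausible reasons for a gap. The protocol's stated hypothesis is that the block reduces pain, morphine use and side effects, so gaps could be more frequent on placebo. Blinded evaluability decisions prevent selection by known allocation. They do not prevent the reasons for missingness from differing between arms.

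Because recruitment runs until 34 are evaluable, excluded patients are replaced and nothing limits how many there can be. At stake are the comparability of the groups as randomised and the loss of usable primary data in a small trial.

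**Working it through.** **Inputs from the protocol.** Control mean 75 mm and SD 20; target difference 20 mm ("a reduction of 20 in the pain score (VAS) will be clinically relevant"); type 1 error 5%, type 2 error 20%; "17 in each group, will be required"; 36 to be included. Five flexion scores fall within 8 h. Two-sided testing is assumed, as sidedness is not stated. The protocol gives no missing-data rate, so every missingness figure below is an assumption.

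**Step 1: the plan's own figure.** The normal approximation gives n = 2 × (1.96 + 0.84)² × (20/20)² = 15.7, so 16 per arm. The two-sample t-test gives 16.7, so 17 per arm and 34 in total, with power 0.807. This matches the protocol. The allowance is 2/36 = 5.6%, and 34/(1 − 2/36) = 36, which also matches. The sample size is not at fault.

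**Step 2: loss if gaps are random.** With independent missingness m per time point, a five-score rule excludes 1 − (1 − m)⁵ of patients; a 4 h rule excludes m.

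| m (assumed) | Excluded, five scores | Of 36 | Excluded, 4 h only | Of 36 |
|---|---|---|---|---|
| 1% | 4.9% | 1.8 | 1% | 0.4 |
| 2% | 9.6% | 3.5 | 2% | 0.7 |
| 5% | 22.6% | 8.1 | 5% | 1.8 |

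Under the five-score rule the allowance of two patients is already exceeded at 2% per time point. Under a 4 h rule it holds even at 5%.

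**Step 3: an unfavourable case at the planned loss.** Suppose 36 are randomised, 18 per arm, and both lost patients are placebo patients with VAS 100. The 16 analysed placebo patients average 75 and the active arm averages 55, so the analysed difference is 20 mm. With the two included, the placebo mean is (16 × 75 + 2 × 100)/18 = 77.8 and the difference is 77.8 − 55 = 22.8 mm. The rule understates it by 2.8 mm.

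**Step 4: pain-driven gaps.** Simulation of five scores per patient, 400,000 patients per arm: means 75 and 55, SD 20, values limited to 0-100, within-patient correlation 0.6 (assumed), 1% missing at VAS 90 or below, and the stated percentage missing above 90 (assumed). Limiting the scale brings the full-data difference to about 19.0 mm.

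| Missing above VAS 90 | Excluded, placebo v active | Difference, all five scores required | Difference, all with a 4 h score |
|---|---|---|---|
| 1% (random only) | 4.9% v 4.9% | 19.0 mm | 19.0 mm |
| 10% | 13.7% v 6.5% | 17.9 mm | 18.7 mm |
| 30% | 28.7% v 9.7% | 15.8 mm | 18.0 mm |
| 50% | 38.4% v 12.1% | 14.0 mm | 16.9 mm |

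In the 30% row, against a full-data value of 19.1 mm, the five-score rule loses 3.3 mm. Using every 4 h score recovers 2.2 mm of that. The remaining 1.2 mm or so comes from missing 4 h scores and is the reason for a sensitivity analysis.

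**Step 5: no treatment effect.** With both means at 75 and 10% or 30% missing above VAS 90, exclusions are equal in the two arms and the bias is about 0.

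**The case against.** Several points in the plan's favour are fair.

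- The rule speaks of data being available, not complete. Requiring all five scores is the natural reading but still an inference. If partial data suffice, the rule does not say how much, so it could not be applied consistently.
- The sample size section ties evaluable patients to the main effect measure. The reach of the exclusion to morphine, nausea, vomiting and sedation is therefore the literal reading of Data processing rather than beyond dispute.
- Exclusions and missing data will be described, and the section on completion and withdrawal asks for an account of non-completers. This gives transparency but corrects nothing.
- Patients are followed for only 24 hours after surgery, and the plan expects to lose two of 36. Real losses may be small.
- Pain-driven gaps act against the block. In null simulations with 21-34% excluded in both arms, type 1 error stayed at 4.6-4.8%, so this mechanism does not manufacture a positive result.

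A reader might go further and infer that the primary comparison is certainly biased, or that power drops to 57-70%. The protocol supports neither. Bias arises only if gaps depend on pain or treatment, and no rate or mechanism is given. Those power figures need 13-26% of placebo and 2-6% of active patients to be excluded, well above the planned 5.6%, and they delete patients from 18 per arm without the replacement that the protocol prescribes. A run closer to the planned loss (7.8% v 1.3% excluded, also assumed) moved the difference from 18.9 to 17.9 mm and power from 79% to 73%.

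What survives is that the rule throws away observed primary-endpoint data for no stated benefit and lets a treatment-affected measurement decide who is analysed.

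**Conclusion.** The point holds as a conditional risk created by a rule that the protocol states, and it should be fixed. It does not invalidate the design. The window is wider than the primary endpoint needs, inclusion depends on a post-randomisation measurement, and replacement is uncapped.

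The direction depends on the mechanism: toward no effect if gaps are driven by pain, about zero bias with lost data if they are random, and possibly the other way under mechanisms not modelled here. The size cannot be fixed from the protocol. It is up to about 2.8 mm in the case worked at the planned loss, and larger only if losses exceed that allowance. These conclusions assume the five-score reading, two-sided testing and the missingness rates set out above.

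**What to change.** Replace the evaluability sentence under Data processing so that:

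- all randomised patients are analysed in the group assigned;
- the primary analysis uses every patient with a 4 h flexion VAS;
- each secondary endpoint uses all patients with data for that endpoint;
- the 0-8 h set is kept only as a sensitivity analysis;
- accrual ends on the number randomised (36), not the number evaluable.

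Record in the CRF the reason for each missed flexion score. Prespecify a sensitivity analysis for missing 4 h scores, for example worst rank for patients unable to flex for any reason related to pain, sedation or nausea. Worst rank is itself a debatable assumption, and applying it to pain alone would leave out the other treatment-related reasons, so it belongs in a sensitivity analysis and not in the primary one. The exclusion after opening a code envelope should be worded to agree with the new analysis set.

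The cost is a few sentences, one CRF field and a little more analysis. The required 34 does not change. If all 36 have a 4 h score and split evenly, t-test power is 0.830 at 18 per arm against 0.807 at 17. The change should be made before the code is broken, since a later change to the analysis set would not be credible.
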